PETNECK2 will examine the effectiveness of PET-CT imaging - introduced at one year after completion of treatment – to determine patients at low risk of recurrence. We hypothesise that this PET-CT scan may identify some patients with asymptomatic recurrence (allowing earlier intervention with salvage therapies), but also those at very low risk of future recurrence. These low-risk patients would then receive a face-to-face education session along with an Information and Support (I&S) resource package, which includes information regarding symptom monitoring, and how to initiate an urgent appointment if they have any concerns or recurrence is suspected. Therefore, instead of regular scheduled follow-up appointments, patients would be in control of when they return for follow-up visits (patient-initiated follow-up).

This programme of work included development of a bespoke I&S resource package [35–37] and an initial feasibility study to optimise the education session and I&S resource package given prior to the phase III Randomised Controlled Trial (RCT), which will formally assess the efficacy and cost-effectiveness of this patient-initiated active surveillance strategy compared to the current standard of care routine scheduled clinical follow-up.

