### Intervention

#### Feasibility study and comparator arm of randomised controlled trial

A PET-CT scan is offered to patients at approximately 12 months following completion of treatment (within 11–14 months). Clinical, radiological and pathological staging is performed according to the UICC TNM Classification of Malignant Tumours staging manual 8th edition [40].

If the PET-CT scan is positive or equivocal for head and neck cancer recurrence, patients will undergo further investigations (as per UK guidelines) to confirm or exclude recurrence (this may include undergoing additional scans, biopsies or examination under anaesthetic). If recurrent cancer is confirmed, they will be treated according to the recommendations of the local multidisciplinary team. Any patient with recurrent cancer should receive scheduled follow-up appointments arranged by their treating clinical team.

If the PET-CT scan is positive but suggests a pathology not thought to represent a HNC recurrence (e.g. a new non-head and neck cancer, or metabolic activity from a non-oncogenic process), further investigations will be offered to the patient guided by the local clinical teams, and a management plan for the patient will be decided based on national guidelines. The patient will still be able to continue with the intervention arm if they wish to.

If the PET-CT scan is negative (with no signs of recurrence or metastases), patients receive an education session delivered by a clinical nurse specialist or Allied Health Professional (APH) (approximately 20–30 min in length) to discuss, demonstrate, and ensure familiarity with the I&S resource.

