#### Control arm of randomised controlled trial

Standard of care clinical follow-up as per UK HNC guidelines is followed at the discretion of the participating centre, e.g. two-monthly in the second year after the end of treatment, and three-to-six monthly in years three-to-five.

The schedule of events for patients in either the PETNECK2 feasibility study and RCT have been included in Tables 1 and 2, respectively.

**Table 1 Tab1:** PETNECK2 feasibility study patient pathway

Assessments	6–14 months post- treatment	Baseline 11–14 months post-treatment	Post PET-CT scan	Follow-up appointment (1–2 months post education session)	Open urgent appointment^a^
Informed consent	x				
Registration	x				
Quality of Life & Resource Use Questionnaires^b^		x		x	
PET-CT scan^c^		x			
PET-CT consultation			x		
PETNECK2 Education Session			x		
Qualitative interview				x	
Clinical Interaction for Symptom Assessment and evaluation					x

^**a**^Multiple and at any time point after the education session for the duration of the feasibility study

^b^To include EQ-5D-5L, EORTC QLQ-C30 and H&N43, Fear of Cancer Recurrence

^c^If recurrent disease diagnosed on PET-CT and confirmed on further investigation, no further study intervention will be undertaken. Follow-up data will still be collected

**Table 2 Tab2:** PETNECK2 randomised controlled trial patient pathway

Assessments	6–14 months post-treatment	Baseline 11–14 months post- treatment	Post PET-CT scan	Open urgent appointment^d^	6 months* follow-up	12 months* follow-up	24 months* follow-up
Informed consent	x						
Registration	x						
Randomisation		x					
Fear of Cancer Recurrence (FCR) questionnaire		x				x	x
EORTC questionnaires (QLQ-C30 and QLQ-H&N43)		x				x	x
EQ-5D-5L & Resource Use questionnaires		x			x	x	x
Self-efficacy & motivation questionnaire		x			x	x	
CQC question					x	x	x
Blood, oral rinse, and tissue collection^b^		x				x	
Fear of Cancer Recurrence interview^c^		x				x	
PET-CT scan^a^		x					
PET-CT consultation^a^			x				
PETNECK2 Education Session^a^			x				
Clinical interaction for sympton assessment and evaluation				x			

^a^Patients randomised to intervention arm only

^b^Optional - patients consenting to PETNECK2 Collect sub-study

^c^Optional - a subset of patients with clinically significant FCR (taken from baseline FCR questionnaire with cut-off ≥ 22) consenting to FCR interviews. The first of these should take place before the PET-CT scan

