### Statistical analysis plan

The median overall survival time and one year (post study entry, i.e., two-year follow-up) overall survival rate for each arm will be reported. These will be calculated using the Kaplan-Meier method of estimation and presented with confidence intervals. A stratified (for stratification factors and any other key prognostic indicators e.g., smoking status) Cox proportional hazards model will be used to determine the hazard ratio and associated confidence interval, which will be evaluated against the non-inferiority margin. Analysis populations will include intention to treat (ITT), modified intention to treat (mITT) and per protocol (PP) to confirm if conclusions are consistent across the analyses. The PP analysis population will be defined as the primary analysis in this case as it is a non-inferiority study. Numbers of patients who drop out or cross over from the intervention to control will be evaluated and used to determine their inclusion in the analysis populations. Analyses that account for treatment switching will be considered if patients in the intervention arm have comparable follow-up profiles to the control. If non-proportional hazards are observed, then models accounting for non-proportional hazards will be considered and explored.

Disease free survival and time to recurrence will be presented using Kaplan-Meier plots and analysed using a stratified Cox proportional hazards model in similar fashion to the analyses proposed for overall survival. If non-proportional hazards are observed, then relevant methods will be undertaken to evaluate the intervention effect (for example flexible parametric modelling).

Recurrence details (TNM staging, location, further treatment) will be analysed descriptively and tabulated by intervention arm. Further treatments (i.e., curative intent, palliative intent, and best supportive care) will be compared between the two arms.

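### Per-protocol is the only primary population for the non-inferiority test, and its membership can depend on crossover out of the intervention arm, so it is open to one-sided, prognosis-related exclusion

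*Protocol article*

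**What the plan says.** The section Statistical analysis plan evaluates the hazard ratio for overall survival against the non-inferiority margin and lists three populations: "Analysis populations will include intention to treat (ITT), modified intention to treat (mITT) and per protocol (PP) to confirm if conclusions are consistent across the" […]. It then chooses between them: "The PP analysis population will be defined as the primary analysis in this case as it is a non-inferiority study". No rule follows that ITT must also meet the margin, or for the case where the populations disagree.

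On who belongs to each analysis set, the same section says: "Numbers of patients who drop out or cross over from the intervention to control will be evaluated and used to determine their inclusion". Intervention to control is the only direction of crossover named. Analyses that account for switching are to be considered if intervention patients turn out to have follow-up like that of controls.

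Three design features bear on this:

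- Table 2, footnote a, restricts the PET-CT, the PET-CT consultation and the education session: "Patients randomised to intervention arm only".
- The Intervention section describes what follows the scan: "If the PET-CT scan is positive or equivocal for head and neck cancer recurrence, patients will undergo further investigations". If recurrence is confirmed: "Any patient with recurrent cancer should receive scheduled follow-up appointments arranged by their treating clinical team". The sub-heading over this text mentions the comparator arm, but the text itself and Table 2 place the pathway in the intervention arm. I read the sub-heading as a labelling slip.
- The Background expects that "this PET-CT scan may identify some patients with asymptomatic recurrence". It gives no prevalence.

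The primary outcome is death from any cause, timed from randomisation.

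**The concern.** The stated reason for making PP primary is that the trial tests non-inferiority. That reason is not enough. PP is a useful guard when non-adherence blurs a real difference, but it is not conservative by nature. If exclusions fall on one arm and are related to prognosis, the comparison loses the protection of randomisation and can move towards non-inferiority.

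The structure for such exclusions is present here. The scan finds occult recurrence in the intervention arm only. Patients with confirmed recurrence then receive scheduled follow-up, which resembles control care. Controls with the same occult disease have no scan at that point, cannot be identified, and stay in. A rule that bases inclusion on observed movement from intervention to control could therefore remove patients at high risk of death from one arm. At stake is the primary conclusion of a trial of reduced surveillance with mortality as its endpoint.

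**Working it through.** **Inputs from the protocol article.** Control survival 94% at 12 months; margin 5 points, HR 1.88; one-sided alpha 2.5%; power 85%; 90 events; 662 patients, 698 after 5% dropout (all from Sample size determination); 1:1 allocation, 33 months of recruitment, at least 12 months of follow-up (Randomised controlled trial).

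**The plan's own figures first.**

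- Margin: ln(0.89)/ln(0.94) = 1.883 (stated 1.88).
- Events (Schoenfeld): 4 × (1.960 + 1.036)² / (ln 1.883)² = 89.6, so 90.
- Expected events: monthly hazard λ = −ln(0.94)/12. With uniform accrual, P(event) = 1 − [exp(−12λ) − exp(−45λ)]/(33λ) = 0.1356, and 662 × 0.1356 = 89.8.
- Dropout: 662/0.95 = 696.8, so 697, or 698 for equal arms.

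The design reproduces. The point concerns the analysis set, not this arithmetic.

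**Where the decision turns.** With 90 events the standard error of ln HR is about 2/√90 = 0.211. The upper limit is below 1.883 when the observed HR is below 1.883 × exp(−1.96 × 0.211) ≈ 1.25.

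**Illustration of one-sided exclusion.** Two quantities are assumed, because the documents give neither: q, the share of patients in each arm with PET-detectable recurrence, and their 12-month mortality m in the control arm, taken as 30%. Overall control survival is held at 94%, so survival in the remaining patients is (0.94 − 0.7q)/(1 − q).

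Hand check for q = 5% and a true HR of 1.0: (0.94 − 0.035)/0.95 = 0.9526. Dropping the recurrences from the intervention arm only gives a 12-month cumulative hazard ratio of ln(0.9526)/ln(0.94) = 0.78. The simulated average of 0.82 over the whole follow-up is a little closer to 1, as expected when the high-risk controls die early.

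Simulation: 331 per arm, exponential survival within each risk group, uniform accrual over 33 months plus 12 months, unstratified Cox model, non-inferiority if the upper 95% limit is below 1.883. The HR within risk groups was raised until the marginal HR over all randomised patients was about 1.88, so that the trial sits at its margin. There were 4,000 runs at the margin and 2,000 at HR 1.0.

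| q | m | False non-inferiority, all kept | False non-inferiority, dropped from intervention arm only | Average HR after dropping, true HR 1.0 |
|---|---|---|---|---|
| 2% | 30% | 2.4% | 4.8% | 0.93 |
| 3% | 30% | 2.4% | 7.0% | 0.89 |
| 5% | 30% | 2.7% | 12.9% | 0.82 |
| 5% | 50% | 2.8% | 20% | 0.69 |
| 8% | 30% | 2.4% | 28% | 0.68 |
| 10% | 30% | 3.0% | 47% | 0.60 |

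The simulation error on a rate near 2.5% is √(0.025 × 0.975/4000) = 0.25 points, so the all-kept column agrees with the nominal level. If the PP set keeps these patients, this bias does not arise.

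**The case against.** A reader might infer that the primary test is biased towards non-inferiority as it stands. The documents do not support that. It would require PET-detected recurrences to leave the intervention arm's PP set, and the article nowhere says they do. Scheduled follow-up after confirmed recurrence is the protocol's own pathway, so a patient who follows it is adherent and would ordinarily stay in. Nor does every positive or equivocal scan lead there: further investigation comes first, and only confirmed recurrence does. Patients who return to scheduled visits from anxiety or preference need not have a worse prognosis, so their exclusion could bias either way.

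There is also a sound reason to want PP. Crossover from intervention to control makes the arms more alike and can pull an ITT hazard ratio towards 1, which itself favours non-inferiority when the strategy is truly worse. The article does run ITT and mITT and leaves room for switching analyses. A detailed PP definition is normally left to the SAP, so its absence from a journal article is no fault.

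All of this stands, and it limits the point to a conditional one. It does not remove the two choices that the article does fix: PP alone is primary, and observed crossover out of the intervention arm informs inclusion. An SAP faithful to this text would inherit both. The dilution argument is a reason to require both sets, not to rely on PP alone.

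**Conclusion.** The point holds in conditional form. The primary non-inferiority conclusion rests on one population whose membership depends on post-randomisation behaviour, in an unblinded trial where only one arm has a scan that identifies patients with recurrence. It is therefore open to one-sided, prognosis-related exclusion. If confirmed PET-detected recurrences were treated as crossovers and left out, the test would be anti-conservative. At an assumed 30% 12-month mortality, the false non-inferiority rate would be about double the nominal 2.5% for q = 2% and about 13% for q = 5%. If they are kept, this mechanism contributes nothing.

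The direction follows from the design. The size rests on q and m, which are assumptions, and on a common hazard ratio in both risk groups. The larger values of q show sensitivity and are not predictions: patients with clinical symptoms or signs of recurrence are not eligible, and the documents give no basis for choosing a value.

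**What to change.** 1. Make ITT (all randomised patients, as allocated) co-primary with PP. Declare non-inferiority only if the upper confidence limit of the hazard ratio is below 1.88 in both. Because both must succeed, no adjustment of alpha is needed.
2. State that PET-detected recurrence, and the return to scheduled follow-up that the pathway then specifies, are not protocol deviations. These patients stay in the intervention arm in every analysis set.
3. Replace the sentence that lets observed dropout and crossover numbers determine inclusion with pre-specified exclusion criteria that apply alike to both arms.

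The change is to protocol and SAP wording only; it should be made before any comparative survival data are seen. The cost is a small loss of power: the chance of passing both analyses cannot exceed the lower of the two separate powers. The loss should be modest because the sets would share most of their patients, but I have not computed it.

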## Background

Head and neck cancer (HNC) is the sixth most common cancer worldwide, with 640,000 cases diagnosed annually [1]. There are 12,000 new cases diagnosed and > 4000 deaths annually in the United Kingdom [2]. Approximately 40% of patients (range 20–57%) treated for HNC commonly develop cancer recurrence at the primary site or the draining lymph nodes [3]. The majority occur in the first two years after treatment (62% in first year, 82% within two years) [4–6]. Rates of distant metastases are reported to be between 10 and 20% [7, 8]. Despite significant morbidity, salvage surgery provides the best opportunity for long-term survival in patients with recurrent HNC, but this is only possible if the recurrent disease is amenable to resection, which is more likely to be the case with early detection [9, 10].

The most recent UK national head and neck cancer guidelines recommend that patients undergo clinical follow-up every two months for the first two years after treatment, and then every three-to-six months for the next three years [11]. Regular follow-up with clinical examination for a minimum of five years following treatment end is also a standard recommendation from almost all international head and neck cancer societies.

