Despite being the international standard, current strategies for HNC surveillance lack a robust evidence base for their effectiveness or efficiency and are inflexible. The rate of cancer recurrence detection in asymptomatic patients through routine clinical surveillance is low [12], with published data suggesting only between 27 and 51% of patients with recurrence can be offered salvage treatment [13, 14]. Importantly, patients are calling for more flexible, patient-centred follow-up [15], with HNC patients reporting current follow-up regimes being too frequent, favouring intensive follow-up in the first year only, with less intensive, symptom-based appointments thereafter [16]. However, this is balanced by HNC patients’ concern that their cancer may return or progress [17, 18]. This fear of cancer recurrence (FCR) has a major impact on patients’ overall quality of life [19, 20] and is well documented in HNC patients [18, 20–22], yet no studies have examined the effect of different follow-up regimens on FCR. Furthermore, this is coupled with limited, poor quality, retrospective and conflicting evidence regarding the relative efficacy of the current strategy of routine follow-up versus symptom-driven self-referral strategies in clinical HNC management: four studies report a difference in overall survival between routine follow-up and self-referral for HNC patients [23–28]. Adding to this issue is the dramatic and exponential rise in the incidence of oropharyngeal squamous cell carcinoma (OPC) driven by human papillomavirus (HPV) infection [29–31], which has higher survival rates [2]. Taken together this contributes to a rapidly enlarging cohort of cancer survivors requiring follow-up, placing significant pressure on finite health care resources [32].

As demonstrated by the PET-NECK trial, positron emission tomography-computed tomography (PET-CT) scans at three months post chemoradiotherapy are an effective strategy to select patients for ongoing management - avoiding a routine neck dissection (the previous standard of care) in > 80% of patients, with a reduction in harm, and saving of £1,415 per patient to the UK’s National Health Service (NHS) [33, 34]. This has become the standard of care in most countries, and we aim in PETNECK2 to develop and test the efficacy and cost-effectiveness of a better paradigm for post-treatment surveillance for patients with HNC.

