#### Randomised controlled trial

The primary outcome measure is overall survival time defined as the interval between the date of randomisation and the date of death from any cause. Patients who have not died at the time of analysis will be censored at the date when they were last known to be alive. Follow up for survival will be collected on trial Case Report Forms (CRFs), by linking with NHS Digital and other health registries and annual hospital record checks.

Secondary outcome measures include:

Cost-effectiveness as measured by incremental cost per quality-adjusted life year (QALY) gained (combining EQ-5D-5L utility scores with overall survival data), and resource use data collection, including number and reasons for healthcare visits.Recurrence and distant metastasis encompassed by:
Disease free survival time defined as the interval between the date of randomisation and the date of a contributing event (either a recurrence (to include local, regional, and distant) or death from any cause and excluding any new primary cancer). Patients who are alive and disease-free at the time of analysis will be censored at the date when they were last known to be alive and disease-free.Time from treatment to first detection of recurrence defined as the interval between the completion of the patient’s definitive preliminary treatment (not including any neck dissection that might have been implemented at three months) and a recurrence of any nature (local, regional, or distant). Patients who die before a recurrence will be censored at their date of death.Details of recurrences, including location (specific details on site and whether local, regional, or distant), TNM stage at detection of recurrence and subsequent treatment for recurrence.
Quality of life assessed by the EORTC-QLQ-C30, EORTC QLQ-H&N43, and EQ-5D-5L questionnaires.Fear of cancer recurrence assessed quantitively by the FCR questionnaire and qualitatively by patient interviews.Patient experience measured by the CQC patient experience question.Patient self-efficacy and motivation will be assessed using responses from the individual self-efficacy and motivation questions.Time to receiving an urgent review appointment, as well as the number and timings of appointments requested (for patients in the intervention arm only).

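### The between-arm comparison of treatment for recurrence states no denominator; read naturally it is made among detected recurrences, a subset the intervention can itself change

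*Protocol article*

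**What the plan says.** In the Protocol article, the secondary outcomes of the randomised trial include details of recurrences, among them "TNM stage at detection of recurrence and subsequent treatment for recurrence". The section Statistical analysis plan then has two consecutive sentences on these data. The first is descriptive: "Recurrence details (TNM staging, location, further treatment) will be analysed descriptively and tabulated by intervention arm". The second goes further: "Further treatments (i.e., curative intent, palliative intent, and best supportive care) will be compared between the two arms". Neither names a denominator, a test or an effect measure.

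In Table 2, the PET-CT scan, the PET-CT consultation and the education session carry the footnote "Patients randomised to intervention arm only". The control arm keeps scheduled clinic visits. In the intervention arm, patients with a negative scan start their own visits instead. The Background expects the scan to alter detection: "this PET-CT scan may identify some patients with asymptomatic recurrence (allowing earlier intervention with salvage therapies".

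**The concern.** Treatment intent has a value only for a patient whose recurrence has been found. The three categories (curative, palliative, supportive) leave no place for a patient without recurrence, so they add up to 100% only among recurrences. A reader of the plan would therefore expect percentages among recurrences, set side by side by arm.

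Being a detected recurrence is a post-randomisation state, and the two arms look for recurrence differently: one scan and then patient-initiated visits, against scheduled visits. Randomisation does not protect a comparison within that subset. Extra early detections in the intervention arm would raise its curative share even if no patient's course changed. Recurrences not yet found under patient-initiated follow-up would drop out of the denominator. Earlier salvage is part of what the trial hopes the scan will achieve, so readers are likely to look to this table for the mechanism.

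**Working it through.** The plan gives no figure for this comparison, so there is none to reproduce. The check asks how far the share among recurrences can move when the number of patients with non-curative recurrence is identical in both arms.

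**Inputs from the Protocol article**
- Patients per arm: 698 randomised 1:1, so 698/2 = 349.
- Curative share under routine care, from the Background: "only between 27 and 51% of patients with recurrence can be offered salvage treatment".
- Recurrence overall, from the Background: "Approximately 40% of patients (range 20–57%) treated for HNC commonly develop cancer recurrence", with 62% of recurrences in the first year and 82% within two years.

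**Assumptions (not in the documents)**
- Both arms have the same underlying recurrences and there is no treatment benefit.
- Some further recurrences are counted in the intervention arm by the time of analysis, and all of them are treated with curative intent.

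**Step 1: plausible number of recurrences per arm.** With 40% recurring overall, 0.40 × 0.62 = 24.8% recur in year one and 0.40 × 0.20 = 8.0% in year two. Among patients free of recurrence at one year, the second-year risk is 8.0/(100 − 24.8) = 10.6%, or about 37 of 349. With 20% or 57% overall it is 4.6% (about 16) or 17.6% (about 62). This ignores deaths and assumes that the quoted timing applies to the trial population. A count of 50 lies inside this range.

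**Step 2: worked example.** Control has 50 recurrences, 20 treated with curative intent and 30 not. The intervention arm has the same 50 plus *k* extra.

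| Extra (*k*) | Curative share among recurrences | Curative per randomised | Non-curative per randomised |
|---|---|---|---|
| 0 (control) | 20/50 = 40.0% | 20/349 = 5.7% | 30/349 = 8.6% |
| 2 | 22/52 = 42.3% | 22/349 = 6.3% | 30/349 = 8.6% |
| 6 | 26/56 = 46.4% | 26/349 = 7.4% | 30/349 = 8.6% |
| 10 | 30/60 = 50.0% | 30/349 = 8.6% | 30/349 = 8.6% |

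**Step 3: range.** Let *c* be the control share and *x* the extra recurrences as a fraction of the control number. The intervention share is (*c* + *x*)/(1 + *x*), so the difference is *x*(1 − *c*)/(1 + *x*). This does not depend on the number of recurrences.
- Smallest, *x* = 0.10 and *c* = 0.51: 0.10 × 0.49/1.10 = 4.5 points.
- Largest, *x* = 0.30 and *c* = 0.27: 0.30 × 0.73/1.30 = 16.8 points.

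**Reading.** The share among recurrences moves with detection alone. The non-curative proportion of all randomised patients does not. The curative proportion of all randomised patients also rises (5.7% to 8.6% in the last row). It is a randomised comparison, but it cannot be read as benefit by itself.

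**The case against.** The strongest reply is that the plan fixes no denominator. Counts of each treatment over all randomised patients would satisfy the sentence as written, and a statistical analysis plan that is not shown may already say so. The preceding sentence names further treatment among the descriptive data. Where inference is intended, the article usually names the method: Cox models, a t-test, linear regression or Poisson regression. All of this stands. A reader might infer that the plan commits itself to a biased test among recurrences; the text does not support that. What remains is that the second sentence singles out treatment intent to be compared, and that the outcome definition and categories lead to recurrences as the base.

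The illustration is also favourable to the concern. If the scan only finds earlier what the control arm finds later within follow-up, there are no extra recurrences by the end, and a shift from palliative to curative intent would be the mechanism of interest. That is fair. However, minimum follow-up is 12 months, so lead time can still leave the counts unequal when the data are analysed.

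Finally, using all randomised patients is only a partial cure. The curative incidence still responds to detection, and a recurrence never found is missing from any numerator. This too stands, and it is why overall survival must be read alongside.

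**Conclusion.** The point holds as a recommendation on a secondary outcome. The wording leads naturally to a contrast among detected recurrences. That contrast could differ by about 4.5 to 16.8 percentage points with no difference in non-curative recurrence, if extra detections amount to 10 to 30% of the control number and all are treated with curative intent. Those fractions are assumptions; the documents give no detection yield for the scan.

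Two stronger readings are not supported. First, a reader might conclude that the trial arms are not comparable. They are randomised and remain so; only the recurrence subsets may differ. Second, a reader might take fewer incurable recurrences to be the hypothesis on which the trial is judged. The Background mentions earlier salvage only as something the scan may allow, and the trial is judged on non-inferiority of overall survival, an endpoint that does not depend on how recurrence is detected. The primary analysis and sample size are untouched.

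**What to change.** State that any between-arm comparison of treatment for recurrence uses all randomised patients, with time measured from randomisation. For each arm, give the cumulative incidence of recurrence treated with non-curative intent (palliative or supportive) and, beside it, of recurrence treated with curative intent. Give the between-arm difference and 95% CI for each. Treat death without recurrence as a competing event. Handle censoring in the estimator rather than using a simple 24-month proportion, because some patients will have only 12 months of follow-up.

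Add one sentence saying that the curative-intent incidence can rise through detection alone and is to be read together with the non-curative incidence and overall survival. Keep percentages among recurrences as description only, labelled as such and without a test.

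The cost is a change of wording and a little more analysis. The data are already being collected.
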